## Abstract

**Introduction:**

Pancreatic cancer is a leading cause of cancer deaths worldwide. Screening for this disease has potential to improve survival. It is not feasible, with current screening modalities, to screen the asymptomatic adult population. However, screening of individuals in high-risk groups is recommended. Our study aims to provide resources and data that will inform strategies to screen individuals with new-onset diabetes (NOD) for pancreatic cancer.

**Methods and analysis:**

The United Kingdom Early Detection Initiative (UK-EDI) for pancreatic cancer is a national, prospective, observational cohort study that aims to recruit 2500 individuals with NOD (<6 months postdiagnosis) aged 50 years and over, with follow-up every 6 months, over a 3-year period. For study eligibility, diagnosis of diabetes is considered to be clinical measurement of haemoglobin A1c ≥48 mmol/mol. Detailed clinical information and biospecimens will be collected at baseline and follow-up to support the development of molecular, epidemiological and demographic biomarkers for earlier detection of pancreatic cancer in the high-risk NOD group. Socioeconomic impacts and cost-effectiveness of earlier detection of pancreatic cancer in individuals with NOD will be evaluated. The UK-EDI NOD cohort will provide a bioresource for future early detection research to be conducted.

**Ethics and dissemination:**

The UK-EDI study has been reviewed and approved by the London-West London and GTAC Research Ethics Committee (Ref 20/LO/0058). Study results will be disseminated through presentations at national and international symposia and publication in peer-reviewed, Open Access journals.

Strengths and limitations of this studyUnited Kingdom Early Detection Initiative will generate the first UK cohort of individuals with new-onset diabetes, designed specifically with the intention of facilitating earlier detection of pancreatic cancer.The study is designed to obtain pre-diagnostic data and biospecimens from pancreatic cancer patients and controls.Prediagnostic samples and data will be generated for the validation of existing early detection biomarkers and for future biomarker discovery.The study will apply health economic models to quantify the costs and benefits of detecting pancreatic cancer earlier in individuals with new-onset diabetes.It is anticipated that approximately 1% of the cohort of 2500 individuals will have underlying pancreatic cancer, generating a limited number of case samples.

## Introduction

Pancreatic ductal adenocarcinoma (PDAC) has the bleakest outlook in terms of survival of all common cancers. The current UK 5-year survival rate of 7.3% has improved only slightly in 40 years.^1 2^ Late disease presentation is the main contributor to high mortality rates, with approximately 85% of individuals not suitable for potentially curative therapy due to locally advanced or metastatic disease. Where surgery is possible, overall survival is significantly increased.^3^ Rapid intervention through earlier detection is key to improving prognosis. With a relatively low incidence rate, population-wide screening as a route to earlier detection is not justified for PDAC.^4^ Screening is recommended for select high-risk groups; however, this currently represents a minority (~10%) of cases.^5^ There remains a need to robustly characterise other high-risk groups for targeted screening strategies capable of capturing a larger proportion of cases.^6^

Approximately, 40%–65% of individuals with PDAC have diabetes at the time of diagnosis,^7–10^ with the majority being of new-onset (<3 years).^8 10–13^ Occurrence of diabetes in this setting is a paraneoplastic manifestation of PDAC,^14^ and individuals with new-onset diabetes (NOD) over the age of 50 are widely recognised as the highest risk group for PDAC.^6^ The prevalence of pancreatic cancer-related diabetes (PDAC-DM) in this group is approximately 1%.^15^ Consequently, screening all individuals with NOD is not feasible, as any test applied would require near-perfect specificity to avoid large numbers of false positives. Methods that enrich for PDAC-DM within the group of individuals with NOD are urgently needed to aid the development of new, practical screening strategies.

PDAC-DM is a form of type 3c diabetes (T3cDM), a classification that also includes chronic pancreatitis-related diabetes, as well as other aetiologies.^16–18^ T3cDM is associated with rapidly worsening glucose control and significant weight loss.^10 12 19^ Depending on study design, different estimates exist for the prevalence of T3cDM among those diagnosed with diabetes, ranging from 1.8% to 9.2%.^16 20 21^ Molecular biomarkers along with epidemiological and clinical characteristics that enable distinction of T3cDM, or PDAC-DM, among NOD could facilitate screening. To date, most studies aimed at identifying early-stage biomarkers of PDAC have used samples and associated data from patients already diagnosed with PDAC and are, thus, compromised by late changes during tumourigenesis that are not seen in early-stage disease. Tailor-made, prediagnostic cohorts are required to provide the necessary samples and associated data to support effective early detection pathways for this high-risk group.

The UK Early Detection Initiative for Pancreatic Cancer will generate a cohort of individuals with NOD, with the necessary clinical information and associated biospecimens to guide the development of a screening strategy for detection of PDAC-DM among NOD, ensuring its suitability within regional healthcare systems.

## Methods and analysis

### Study setting

The United Kingdom Early Detection Initiative (UK-EDI) Study is a national, prospective, observational cohort study, recruiting individuals with NOD aged 50 years and over to facilitate the development of screening pathways for PDAC. The study will align with a larger international effort, including studies in the USA^22^ and the European Union. The UK-EDI study is hosted by the Liverpool Clinical Trials Centre at the University of Liverpool.

### Dates of the study

From 18 January 2021 to 31 March 2024.

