### Eligibility criteria

Eligibility criteria and relevant definitions of the UK-EDI cohort are provided in table 1.

**Table 1 T1:** Eligibility criteria and relevant definitions of the UK-EDI cohort

Criteria/definition	Details
Inclusion criteria	Aged≥50 years at the time of study entry New-onset diabetes (defined at HbA1c≥48 mmol/mol (6.5%) diagnosed within 6 months of study entry Willing to provide written informed consent prior to performing any protocol-related procedures Willing and able to comply with the protocol for the duration of the study, including scheduled follow-up visits
Exclusion criteria	Diagnosis or treatment of pancreatic cancer, peri-pancreatic cancer, or pancreatic endocrine cancer Previous surgical resection of the pancreas Diagnosis of diabetes>6 months prior to study entry Pregnancy Condition preventing study investigation and follow-up Inability or incapacity to give written informed consent
Definition of new-onset diabetes	HbA1c≥48 mmol/mol (6.5%) diagnosed within 6 months of study entry
Identification of PDAC diagnoses	NHS digital will be interrogated to update occurrence of PDAC

HbA1c, glycated haemoglobin; PDAC, pancreatic ductal adenocarcinoma; UK-EDI, UK Early Detection Initiative for Pancreatic Cancer.

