### Study timeline

Eligible individuals will be provided with a participant information sheet explaining the UK-EDI Study and will be given an opportunity to ask questions prior to signing an informed consent form. At the baseline visit, a full medical, drug and surgical history will be elicited, including demographic, social and anthropometric data. Participants will also be asked about a range of symptoms over the preceding 6–12-month period, which may indicate early signs of PDAC. Participants will be asked specifically about weight changes, including in the context of a weight management programme. Quality of life assessment will be via a health-related Quality of Life Questionnaire (EuroQol Research Foundation: EQ-5D-5L),^25^ and diabetes management will be captured via a Diabetes Self-Management Questionnaire (DSMQ).^26^ The DMSQ is an instrument which assesses diabetes self-care activities associated with glycaemic control. Blood samples will be taken for measurement of haemoglobin A1c (HbA1c) and research plasma and serum samples will be taken for biobanking according to GCP Laboratory standards to allow for translational research. Sites may also provide the results of other haematological and biochemical blood results including full blood count, liver function tests, urea and electrolytes, and lipid profiles, if these are being taken for routine diabetes care. Supplemental blood test results are not required for all participants.

Follow-up visits will be at 6, 12, 18 and 24 months after the baseline visit. Quality of Life, DSMQ and case report form data will be collected at baseline and each follow-up visit. At 36 months, there will be a search of NHS Digital to determine the number of events of PDAC diagnosis in the enrolled cohort.

Key clinical and translational characteristics, including timeframes, of the UK-EDI cohort are listed in table 2.

**Table 2 T2:** Eligibility criteria and relevant definitions of the UK-EDI cohort

Data item	Details
EDTA stored blood	Translational blood samples taken at baseline, 6, 12, 18 and 24 months stored to GCP standards
Serum stored blood	Translational blood samples taken at baseline, 6, 12, 18 and 24 months stored to GCP standards
HbA1c measurements	HbA1c measurements from diagnosis, baseline, 6, 12, 18 and 24 months
Demographics	Details including ethnicity, smoking, and alcohol status
Anthropometric data	Height, weight, waist and hip measurements taken at baseline, 6, 12, 18 and 24 months

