### Statistical methodology

#### Sample size

We aim to recruit 2500 patients with NOD aged 50 years and older, with a follow-up of 36 months. The target size of 2500 is pragmatic, based on costs and what is practically possible. It is anticipated that 0.8%–1% of the group will receive a diagnosis of PDAC in the 3-year follow-up time period.^15^

Thus, the UK-EDI cohort is expected to yield approximately 21–25 PDAC diagnoses (or 17–20 cases with 20% attrition). This study will provide data on the incidence of PDAC in individuals with NOD in the UK and will serve as the benchmark/reference point for future work.

Formal power calculations to determine associations between clinical/biological subgroups and the diagnosis of PDAC are difficult as it is not yet known what fraction of any subgroups will split the available patient population.

The UK-EDI cohort will contribute to larger international efforts aimed at determining the feasibility of detecting resectable PDAC in individuals over 50 years of age who are newly diagnosed with diabetes mellitus.^23^

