#### Data analysis plan

The primary endpoint of interest is clinically diagnosed PDAC within 3 years of a new diagnosis of DM. The measurement of clinical characteristics, including glucose control (HbA1c) along with biological and epidemiological measures at five time points over the course of the cohort study, will help inform the incidence of PDAC in individuals with NOD in the UK.

Analysis of PDAC diagnosis will be performed using longitudinal methods, assessing the effect of biological and epidemiological markers while adjusting for relevant clinical characteristics.

Validation of biomarkers will include receiver operator characteristic curve analysis to determine biomarker performance characteristics. Further exploratory analysis will be carried out using multivariate techniques such as principal component and hierarchical cluster analyses in order to reduce the dimensionality of the data and identify naturally forming groups within the data, respectively.

Secondary analyses will focus on the time to detection of PDAC using a time-to-event approach. The probability of detecting PDAC will be calculated across subgroups using the method of Kaplan-Meier. Inclusion of biological and clinical characteristics will be incorporated using joint survival/longitudinal modelling techniques. Detailed information including clinical, epidemiological and biomarker data will be used to build a PDAC risk score, or validate emerging risk scores.

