## Ethics and dissemination

### Ethical approval

UK-EDI is approved by the UK Health Research Authority with favourable opinion granted by the London-West London and GTAC Research Ethics Committee on 14 February 2020. The details of this manuscript represent V.5 of the protocol approved on the 9 September 2021.

The study will be conducted in accordance with the Human Rights Act 1998, the Data Protection Act 2018, Freedom of Information Act 2000, the principles of GCP, the Declaration of Helsinki on biomedical research involving human volunteers (Hong Kong revision, 1989 and the 48th General Assembly, Somerset West, Republic of South Africa, October 1996, updated in October 2013) and the UK Policy Framework for Health and Social Care Research, where individuals agree to take part in the study, they will be informed of how data are recorded, collected, stored and processed, and that data may be transferred to other countries, in accordance with UK General Data Protection Regulations.

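### The stated study dates (38.4 months) leave room for 36 months of follow-up only for people entering in the first 2.4 months, so the dates, the follow-up and the expected case count do not fit together

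*Protocol article*

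**What the plan says.** All of the following is in the Protocol article.

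- Dates of the study, in full: "From 18 January 2021 to 31 March 2024". The text does not say whether this covers recruitment, funding or the whole study.
- Sample size: "We aim to recruit 2500 patients with NOD aged 50 years and older, with a follow-up of 36 months". The same section continues: "It is anticipated that 0.8%–1% of the group will receive a diagnosis of PDAC in the 3-year follow-up time period". From this it derives the case count: "expected to yield approximately 21–25 PDAC diagnoses (or 17–20 cases with 20% attrition").
- Study timeline: visits with blood samples and questionnaires run to 24 months after baseline. Then: "At 36 months, there will be a search of NHS Digital to determine the number of events of PDAC diagnosis in the enrolled cohort".
- Data analysis plan: "The primary endpoint of interest is clinically diagnosed PDAC within 3 years of a new diagnosis of DM". Under Eligibility criteria (Table 1), diabetes must have been "diagnosed within 6 months of study entry", so the endpoint clock can start up to 6 months before entry.
- Ethical approval: "The details of this manuscript represent V.5 of the protocol approved on the 9 September 2021". The article still describes recruitment in the future tense.

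No accrual period is stated.

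**The concern.** A 38.4-month study that needs 36 months per participant has 2.4 months left for recruiting 2500 people. Two statements in the article point to longer accrual. Under Methods of participant identification, health records are to be searched for eligible people every 6 months, so a second round already falls outside that window. And the version described was approved more than 5 months after 31 March 2021, with recruitment still written as a future activity.

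Three things are at stake if observation really ends on 31 March 2024. The expected number of cases would be too high, in a study where each case counts. The 3-year incidence, which the Sample size section offers as a reference point for later work, would rest on incomplete windows. And people treated as controls in the biomarker analyses would include some whose 3-year window had not closed. The 24-month samples of late entrants are a separate loss.

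**Working it through.** **The plan's own figure.** Expected cases = N × 3-year risk. 2500 × 0.008 = 20 and 2500 × 0.01 = 25. With 20% attrition: 20 × 0.8 = 16 and 25 × 0.8 = 20. The stated 21–25 and 17–20 are reproduced closely. The lower ends correspond to a risk of 0.84% (2500 × 0.0084 = 21; 21 × 0.8 = 16.8). That small difference does not bear on this point, and 21–25 is used below. The calculation gives every participant the full 3-year risk.

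**Calendar.** 18 January 2021 to 31 March 2024 is 1168 days; 1168 / 30.4375 = 38.4 months.

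- 36 months from baseline: 38.4 − 36 = 2.4 months for entry, to 31 March 2021. Recruiting 2500 in those 72 days needs about 1057 per month.
- 3 years from diabetes diagnosis: the last entry date is 31 March 2021 for someone diagnosed at entry and about 30 September 2021 for someone diagnosed 6 months earlier. The later date gives 8.4 months, or about 298 per month.
- 24-month visit: 38.4 − 24 = 14.4 months for entry, to 31 March 2022.
- Entry on or after 9 September 2021, the approval date of V.5: at most 934 days, or 30.7 months, from entry.

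**Yield if observation stops on 31 March 2024.** The article gives neither accrual length nor hazard shape, so both are assumptions: uniform entry over A months from 18 January 2021 and events spread evenly over 36 months from entry. For A above 2.4 months (2.37 unrounded):

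mean follow-up = 36 − (A − 2.37)² / (2A); yield = (21 to 25) × mean follow-up / 36.

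For A = 12: 36 − 9.63² / 24 = 32.1 months; 32.1 / 36 = 0.893; 21 × 0.893 = 18.7 and 25 × 0.893 = 22.3.

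| Accrual A (months) | Reach 36 months from entry | Mean follow-up (months) | Fraction of cases seen | Cases before attrition |
|---|---|---|---|---|
| 6 | 39.6% | 34.9 | 0.970 | 20.4–24.2 |
| 12 | 19.8% | 32.1 | 0.893 | 18.7–22.3 |
| 14.4 | 16.5% | 31.0 | 0.861 | 18.1–21.5 |
| 24 | 9.9% | 26.3 | 0.729 | 15.3–18.2 |

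Applying the same fractions to the plan's 17–20 gives 15.2–17.9 cases for A = 12 and 12.4–14.6 for A = 24.

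**Sensitivity.** If half of the events fall in the first year, A = 24 gives 16.7–19.9. If everyone enters 6 months after diagnosis, so that the same 21–25 cases fall within 30 months of entry at a constant rate, A = 12 gives 20.6–24.5 and A = 24 gives 17.4–20.8.

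**The case against.** The strongest reply is that the dates line is a single sentence that does not say what it covers, and that the 36-month step is a records search which needs no visit. It could be run after 31 March 2024, and the yield would then be untouched. This is fair, and it is why the shortfall is conditional. But the article does not say that linkage continues past the end date, and a later search could not recover 24-month samples that were never taken.

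Three stronger readings are tempting, and the document does not support them.

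- A reader might infer that the primary endpoint fails for everyone who enters after 31 March 2021. It does not: the endpoint runs from diabetes diagnosis, so some entrants up to about 30 September 2021 can complete it within the dates. After that nobody can.
- A reader might infer that 21–25 cases cannot be delivered. That depends on accrual length, hazard shape and the date of the search. With accrual of 6 months or less the loss is under one case.
- A reader might infer that the plan reports a crude 3-year proportion with incomplete participants counted as free of PDAC. No section says so. The Data analysis plan includes Kaplan-Meier and joint modelling, which can handle incomplete follow-up, and the search timing follows visits counted from baseline, so a search at each participant's own month 36 is a natural reading. However, the time-to-event work is labelled secondary, no censoring date is given, and the planned ROC analysis has no stated handling of open windows. Study month 36 (18 January 2024) also falls inside the dates, so a single search at that point is not excluded.

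Finally, the target of 2500 is declared pragmatic and no power claim depends on the yield. This limits the consequence but does not remove the contradiction.

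**Conclusion.** The point holds as a contradiction between the stated dates and the stated follow-up, and it needs correcting. The calendar result needs no assumption beyond reading the dates as the limits of the whole study: the 36-month, endpoint and 24-month-visit requirements each fit only for early entrants.

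The effect on the yield is conditional on observation stopping on 31 March 2024. With uniform accrual and a constant hazard from entry, the expected count falls by about 2.3–2.7 cases for 12-month accrual (21 − 18.7; 25 − 22.3) and by about 5.7–6.8 for 24-month accrual (21 − 15.3; 25 − 18.2). The loss is smaller if events come early or if people enter well after diagnosis. Under the same stop date, some biomarker controls would lack a complete 3-year window.

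**What to change.** Reconcile the Dates of the study, Study timeline, Sample size and Data analysis plan sections. State what the dates cover and the accrual period. Set the final NHS Digital linkage cut-off at least 36 months after the last participant's baseline, which is enough whether the clock starts at entry or at diabetes diagnosis. Say that the search covers each participant's own window. Reconcile the end date for visits separately, because later linkage does not restore the 24-month visit for anyone entering after 31 March 2022.

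If 31 March 2024 is fixed, make the time-to-event estimate, with administrative censoring at that date, the basis for the 3-year incidence. Handle censoring in the ROC analyses, and restate the expected cases from the planned accrual.

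The cost is a change of wording plus either longer passive record linkage with a later final read-out, or a lower stated yield. Keeping all 24-month visits under longer accrual would also mean visits continuing after the stated end date.

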### Study design

The UK-EDI Study has seven work packages (WPs) centred on the establishment of the UK-EDI cohort (WP1, figure 1). Additional WPs include banking of blood samples to the standards of Good Clinical Practice (GCP) for laboratories (WP2), validation of existing promising biomarkers for their ability to distinguish T3cDM, including PDAC-related DM, from T2DM (WP3), interrogating epidemiological and demographic factors to further stratify risk of PDAC in the NOD population (WP4), undertaking new biomarker discovery (WP5), cost-benefit analysis (WP6) and managing and engaging stakeholders (WP7). The primary aim of the UK-EDI Study is to gather and interrogate key data to advance early detection of occult PDAC in the high-risk population of individuals with NOD.

**Figure 1 F1:**
[figure not shown]
UK Early Detection Initiative for Pancreatic Cancer (UK-EDI) Programme outline. NOD, new-onset diabetes mellitus; PDAC, pancreatic ductal adenocarcinoma; T2DM, type 2 diabetes mellitus; T3cDM, type 3c diabetes mellitus; WP, work package.

For pragmatic reasons, the UK-EDI study does not contain an imaging component. A similar trial underway in the USA, designed to improve detection of operable PDAC in individuals with NOD, includes an imaging arm.^23^ In that study, the Enriching New-onset Diabetes for Pancreatic Cancer (ENDPAC) algorithm risk stratifies individuals with NOD based on age and changes in both weight and diabetes parameters.^23^ Individuals with high ENDPAC scores are stratified to the intervention arm.

### Eligibility criteria

Eligibility criteria and relevant definitions of the UK-EDI cohort are provided in table 1.

**Table 1 T1:** Eligibility criteria and relevant definitions of the UK-EDI cohort

Criteria/definition	Details
Inclusion criteria	Aged≥50 years at the time of study entry New-onset diabetes (defined at HbA1c≥48 mmol/mol (6.5%) diagnosed within 6 months of study entry Willing to provide written informed consent prior to performing any protocol-related procedures Willing and able to comply with the protocol for the duration of the study, including scheduled follow-up visits
Exclusion criteria	Diagnosis or treatment of pancreatic cancer, peri-pancreatic cancer, or pancreatic endocrine cancer Previous surgical resection of the pancreas Diagnosis of diabetes>6 months prior to study entry Pregnancy Condition preventing study investigation and follow-up Inability or incapacity to give written informed consent
Definition of new-onset diabetes	HbA1c≥48 mmol/mol (6.5%) diagnosed within 6 months of study entry
Identification of PDAC diagnoses	NHS digital will be interrogated to update occurrence of PDAC

HbA1c, glycated haemoglobin; PDAC, pancreatic ductal adenocarcinoma; UK-EDI, UK Early Detection Initiative for Pancreatic Cancer.

